### Ethical Considerations

The study received ethics approval from the Child and Adolescent Health Service Human Research Ethics Committee (RGS5295) for Australian sites and from the Northern A Health and Disability Ethics Committee for the New Zealand site (2024 FULL 19738). It was prospectively registered with the Australian New Zealand Clinical Trials Registry (ACTRN12622001293752) on October 6, 2022. Each participating site obtained site governance approval as per their ethics and governance committees. Informed consent will be obtained for all patients, with a waiver of consent for patients after 3 unsuccessful attempts to contact the parent or guardian for retrospective consent. Files containing private or confidential data will be stored only in secured locations accessible only by appropriate designated members of the research team, with all data de-identified before data entry onto the REDCap database. There is no compensation provided to participants.

## Results

The study recruitment process and timeline are shown in Figure 1.

This study received funding in July 2023 and started enrolment in August 2023. At the time of protocol manuscript submission in October 2024, we have enrolled and completed follow-up on 1227 participants with recruitment and data collection expected to be completed by mid-2025. Data analysis is expected to be completed by late 2025, and the expected results to be published in early 2026.

**Figure 1 figure1:**
[figure not shown]
Study process and timeline. CRF: case report form. *Dependent on consent and need for follow up. **Contact for retrospective consent can be performed concurrently with follow up in 30-60 days.

## Discussion

### Principal Findings

The pARC score was the best-performing CPS in the feasibility study through more accurate risk identification and stratification [43], and we hypothesize the pARC score will likewise have higher diagnostic accuracy in our multicenter study compared to other published CPSs.

### Comparison With Previous Work

The inclusion of 30 CPSs and the prospective nature of the study, with a planned study size of 2400 patients would make it one of the largest prospective validation studies in children, comparing the largest number of CPSs compared with previous studies [36,39,40,43,44,59,60]. A total of 10 EDs across ANZ will contribute data, including a mix of community and tertiary pediatric centers, which will allow the study's findings to be broadly generalizable across ANZ EDs compared to previous ANZ studies in single centers [6,43,44].

### Strengths and Limitations

Our study will allow the simultaneous comparative application and validation of 30 CPSs for diagnosing pediatric appendicitis outside their derivation settings. In addition to a high recruitment rate, the study will depend on high follow-up rates to ensure that our results accurately represent the whole population of children presenting to the ED with suspected appendicitis, as all patients lost to follow-up will be excluded from data analysis for CPS calculation. Ideally, all patients with abdominal pain would undergo investigations or appendectomy to determine the presence or absence of appendicitis; however, this would increase the rate of unnecessary investigations and potentially the rate of negative appendectomies should investigations be inconclusive. Therefore, a similar methodology to a previous PREDICT study looking at clinical decision rules for head injuries [72] was adapted using follow-up telephone or email contact to establish the presence or absence of appendicitis after discharge from the ED. It is also possible some patients with appendicitis would be treated conservatively with antibiotics and excluded from the study; however, this would represent a small number of patients as this is an uncommon practice in ANZ with only one patient in the feasibility study treated conservatively after a radiological diagnosis of appendicitis due to parental preference [43].

The predictor variables for the 30 CPSs were derived solely from original publications [2-31] and amalgamated into a single case report form developed by the study authors, which may introduce an element of interpretation in terms of the exact clinical terminology used in ANZ ED settings. The difficulty and variability of prospective clinician data collection in busy EDs in completing the case report form may result in a significant proportion of patients with multiple missing variables to calculate all CPSs; however, the feasibility study demonstrated the viability of the case report form used with all study CPSs being calculable in the majority of the patient cohort (ranging from 52% to 93.3%) based on constituent variables available [43]. Implementation of an appropriate method, such as multiple imputation, will be considered to minimize potential biases that may arise from missing data in the multicenter study [73].

Rates of computerized tomography imaging in ANZ EDs are lower than in the United States [74] due to concerns about radiation exposure and associated lifetime risk of malignancy and the more prevalent use of ultrasound in pediatric abdominal pain in Australian EDs [1]. The validation of CPSs in a different setting from those in which most of the CPSs are derived may be a potential key strength of the study and allow study findings to be generalizable across ANZ EDs and similar settings. Finally, one key strength of our study is its assessment of the accuracy of clinician gestalt in diagnosing pediatric appendicitis and comparison with to the best performing CPS, which may provide more compelling evidence to support and encourage the use of CPSs among clinicians for guiding clinical management of suspected appendicitis as part of an ED clinical pathway [75].

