### Objectives

The primary aim of the study is to externally validate various published CPSs for the risk of appendicitis in children aged 5 to <18 years presenting to ANZ EDs with acute abdominal pain and suspicion of appendicitis.

The secondary aims of the study are as follows:

1. To evaluate and compare the performance of various published CPSs:

(A) against clinician gestalt in ANZ for the likelihood of appendicitis at the time of ED assessment;

(B) in identifying, prospectively, the likelihood of complex appendicitis (defined as the presence of perforation, extraluminal fecalith, diffuse intraperitoneal pus, or a well-formed abscess) [62];

2. To describe the epidemiology and management of pediatric appendicitis, illustrating:

(A) The burden of disease in patients presenting with acute abdominal pain with the suspicion of appendicitis;

(B) The incidence and type of surgical procedures undertaken in the management of appendicitis in ANZ (laparoscopic appendectomy, open appendectomy, nonsurgical management with intravenous antibiotics, and delayed appendectomy);

(C) The imaging procedures undertaken in patients assessed for possible appendicitis, and their accuracy in the detection of histologically confirmed appendicitis or surgically confirmed appendicitis in cases where histopathological findings are unavailable.

This will improve the accuracy of diagnosis, reduce health care costs, rationalize the use of health care resources, and improve the management of childhood appendicitis. It will also provide a description of the current diagnostic and management approaches in ANZ for pediatric abdominal pain and appendicitis.

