### Statistics and Interim Analysis

We will follow Standards for the Reporting of Diagnostic accuracy studies (STARD) 2015 guidelines for statistics [69] and the Strengthening the Reporting of Observational Studies in Epidemiology (STROBE) guidelines [70], and validation of CPSs will be performed and reported in according to the 2014 updated methodologic standards for interpreting clinical decision rules in emergency medicine [71]. The AUC will be calculated for the various published CPSs and the clinician's gestalt for the outcome of appendicitis. The sensitivity, specificity, negative predictive value, positive predictive value, negative likelihood ratio, positive likelihood ratio, and missed appendicitis rate will be calculated based on the published cutoffs for each score [2-31]. For the pARC, subanalysis will be performed for the following pARC categories based on previous validation studies [4,56]: ≤5%, 6%-15%, 16%-25%, 26%-50%, 51%-75%, 76%-90%, and >90% for pediatric EDs and <5%, 5%-14%,15%-24%, 25%-49%, 50%-74%, 75%-84%, and ≥85% for mixed ED. For clinician’s gestalt, subanalysis will be performed for each point on the Visual Analog Scale. The AUC will also be calculated for complex appendicitis to assess the optimal cutoffs for each CPS to detect complex appendicitis.

The best-performing CPS will be identified by the highest AUC. Sensitivity and positive predictive value will be calculated to establish the CPS’s ability to identify high-risk patients, and the misclassification rate (proportion of patients identified as low-risk who had acute appendicitis) and negative likelihood ratio will be calculated to establish the CPS’s ability to identify low-risk patients. Accuracy will be reported as the proportion of patients not misclassified as either low-risk or high-risk as defined by published cutoffs. Baseline analyses of patient characteristics based on the risk groups as calculated by the best-performing CPS will be conducted by presenting simple counts and percentages with interquartile ranges.

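### Setting gestalt against whichever of 30 scores has the highest AUC in the same children flatters the score when several perform alike, and no correction is stated

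*Protocol article*

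**What the plan says.** Five places in the protocol article bear on this.

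- Objectives, secondary aim 1A: the performance of various published CPSs is to be compared "against clinician gestalt in ANZ for the likelihood of appendicitis at the time of ED assessment".
- Statistics and Interim Analysis: "The AUC will be calculated for the various published CPSs and the clinician's gestalt for the outcome of appendicitis". The selection rule follows: "The best-performing CPS will be identified by the highest AUC".
- Strengths and Limitations, on the number of candidates: "Our study will allow the simultaneous comparative application and validation of 30 CPSs for diagnosing pediatric appendicitis outside their derivation settings".
- Strengths and Limitations, on gestalt: a key strength is the assessment of gestalt and its "comparison with to the best performing CPS, which may provide more compelling evidence to support and encourage the use of CPSs".
- Principal Findings, on the expected winner: "we hypothesize the pARC score will likewise have higher diagnostic accuracy in our multicenter study compared to other published CPSs".

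The article states no separate sample for selection and comparison, no optimism correction and no multiplicity adjustment for the gestalt contrast. The power statement under Sample Size and Power Calculation concerns one pair of AUCs.

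**The concern.** The two sides of the contrast are not treated alike. Gestalt contributes one AUC. The CPS side contributes the largest of 30 AUCs, chosen in the same children in whom it is then compared. The maximum of several noisy estimates tends to exceed the true value of the score that attains it. When scores are close, part of the winner's lead is therefore selection error, and that error runs towards the CPS.

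The article offers this comparison as evidence to persuade clinicians to use CPSs within ED pathways. At stake is a reported advantage over clinicians that is partly, or in an unfavourable configuration wholly, a product of the selection. This is separate from how the scores rank among themselves; it matters even if that ranking is only descriptive.

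**Working it through.** **Inputs from the article (Sample Size and Power Calculation).** 2400 children, 30% appendicitis, all CPSs calculable in at least half, two-sided alpha 0.05, average correlation between scores of at least 0.5. The count of 30 scores is in Strengths and Limitations.

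**Step 1: reproduce the plan's own figures.**
- Cases: 2400 x 0.5 x 0.30 = 360. Non-cases: 1200 - 360 = 840.
- Hanley-McNeil standard error: SE² = [A(1-A) + (m-1)(Q1-A²) + (n-1)(Q2-A²)]/(mn), with Q1 = A/(2-A), Q2 = 2A²/(1+A), m = 360, n = 840.
- A = 0.75: SE = 0.01637, and 1.96 x SE = 0.0321. A = 0.95: SE = 0.00819, and 1.96 x SE = 0.0160. These match the stated 0.032 and 0.016 as half-widths.
- Power = Φ(|difference|/SEdiff - 1.96), with SEdiff² = SE1² + SE2² - 2r·SE1·SE2. The correlation r between AUC estimates is assumed to be 0.40-0.45. For 0.80 v 0.85 (SEs 0.01515 and 0.01352) the power is 0.89-0.91. For 0.90 v 0.94 it is 0.94-0.96. Both agree with the stated >85% and >90%.

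The sample-size figures are sound, but they describe two AUCs and not a winner of 30.

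**Step 2: the effect of selecting the winner.** Binormal simulation, 1000 runs per setting, with 30 scores and gestalt in the same 360 cases and 840 non-cases. The highest-AUC score is taken and tested against gestalt with a paired DeLong test at two-sided 0.05. No score is truly better than gestalt, so the nominal rate of a false CPS win is 2.5%. Assumptions that the article does not supply: the true AUCs, a correlation of 0.5 between each score and gestalt, and between-score correlations of 0.5-0.9 (all-equal rows) or 0.5-0.8 (other rows). In the all-equal rows the common true AUC is 0.80, 0.85 or 0.90. In the others gestalt is at 0.85.

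| True position of the scores | Winner's mean excess | False CPS win |
|---|---|---|
| All 30 equal gestalt, between-score correlation 0.5 | 0.015-0.021 | 25-26% |
| All 30 equal, correlation 0.8 | 0.009-0.013 | 13-14% |
| All 30 equal, correlation 0.9 | 0.007-0.010 | 9-10% |
| 10 equal, the rest 0.05-0.15 lower | 0.009-0.014 | 8-14% |
| 5 equal, the rest 0.05-0.15 lower | 0.007-0.010 | 5-10% |
| Spread evenly 0.70 to 0.85 | 0.003-0.004 | 3-4% |
| 1 equal, the rest at least 0.05 lower | about 0 | 2.4-2.7% |

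For scale, the largest excess at a true AUC of 0.80 is 0.0205. That is 0.0205/0.05 = 41% of the difference the study is powered for at that level. At 0.90 it is 0.0145/0.04 = 36%. With 1000 runs the Monte Carlo standard error at 2.5% is √(0.025 x 0.975/1000) = 0.5 percentage points, so 3-4% is barely distinguishable from nominal.

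**Step 3: check the remedy.** In the all-equal settings, one score named in advance beats gestalt in 2.1-2.9% of runs, which is nominal. Keeping the winner but testing at 0.05/30 gives 0.0-1.8% across all settings, which is conservative. The bootstrap alternative was not simulated.

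**The case against.** **The persuasive sentence is in the Discussion, and the operative text is broader.** Aim 1A and the statistics section set gestalt beside all the CPSs, pARC included, and no formal test of the winner against gestalt is written down. This stands in part: readers will be able to see every AUC, and the false-win rates above assume a test that the article does not state. But the statistics section does fix the highest-AUC rule, and the winner is the comparator the article puts forward. The upward error in the winner's AUC is there whether or not a test is done.

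**An SAP may deal with it.** It may. The point here is the selection rule and comparator that the article states, not the absence of detail.

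**A reader might infer that gestalt loses by construction.** The documents do not support that. The bias vanishes when one score clearly leads. The article itself points to unequal scores: the Background reports limited clinical utility for the Alvarado score and PAS, and the Discussion says pARC performed best in the feasibility study. A separate simulation of 400 runs per setting, with gestalt correlated with each score as strongly as the scores are with one another (0.5-0.85), gives false wins in 23-28%. That too needs all 30 scores to equal gestalt exactly, so it is close to an upper bound and not an expected rate.

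**The net direction of the whole comparison is not settled.** The case report form allows gestalt to be formed after bloods or imaging, whereas CPSs with radiological parameters are excluded. Some gestalt ratings may therefore use information that no score has, which favours gestalt. This stands. The claim here is only that the selection step pushes towards the CPS.

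**A reader might also infer a second bias at the decision level,** because CPSs are judged at published cutoffs and for gestalt "subanalysis will be performed for each point on the Visual Analog Scale". That does not follow. Every point is reported and none is selected. A point chosen after the results were seen would favour gestalt, not the CPS.

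**Conclusion.** The point holds in a limited form. The stated rule and comparator give a contrast that is optimistic for the CPS when several scores perform close to the best one. If no score is truly better than gestalt, the winner's mean excess runs from about 0 (one clear leader) to 0.007-0.021 (all 30 equal). The false-win rate runs from about 2.5% to 9-26% in the same settings, and is 3-4% when scores are spread from 0.70 to 0.85.

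Where this study falls in that range cannot be read from the documents. The figures rest on continuous, equally correlated binormal scores, a correlation with gestalt of 0.5, and the planned minimum of 360 cases and 840 non-cases. This is a secondary aim and the sample-size calculation is unaffected. It deserves correction because the comparison is offered as a reason for clinicians to adopt CPSs, and the remedy is cheap.

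**What to change.** For secondary aim 1A, make the main analysis a paired AUC comparison of gestalt with pARC in children who have both, and record this before the outcome comparison is seen. The article's stated expectation, "we hypothesize the pARC score will likewise have higher diagnostic accuracy", is relative to other CPSs and not to gestalt, so this is a new prespecification. It draws on the earlier feasibility study and so does not depend on which score wins in this cohort.

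Report gestalt against the empirically best CPS as exploratory. Alternatively, give an optimism-corrected difference and confidence interval from a bootstrap that repeats the highest-AUC selection in each resample.

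The cost is a few sentences of analysis wording, minor extra computing and no new data. The winning CPS will have a slightly less favourable figure. If a score other than pARC wins, its advantage over gestalt will be exploratory or bootstrap-corrected.

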### Conclusion

The study findings and subsequent implementation of CPSs in ANZ EDs have the potential to reduce health care costs, rationalize the use of health care resources, and improve management and outcomes of childhood appendicitis. Implementation of the pARC score in the clinical management pathway for suspected appendicitis at PCH ED has recently been established following the results of the feasibility study, and a postimplementation study is planned to be performed in the future to assess for improvement in patient outcomes through impact analysis testing.

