## Methods

### Overview

The study is an endorsed Paediatric Research in Emergency Departments International Collaborative (PREDICT) network [63] study with Perth Children’s Hospital (PCH) as the lead site. The study is a quantitative multicenter observational study that measures the performance accuracy of CPSs in identifying surgically or histologically confirmed appendicitis. Eligible CPSs (Multimedia Appendix 1) were identified in a rapid review by the study authors before study commencement [43]. Any CPS developed in either pediatric or adult populations was eligible except for: CPSs aiming only to differentiate simple from complex appendicitis or performed only for a subset of children (eg, preschool children and children with chronic illnesses); CPSs requiring variables unlikely to be routinely collected in a pediatric population identified a priori through consensus agreement by study authors (eg, rectal examination, biomarkers other than full blood picture, or C-reactive protein); and CPSs that included radiological parameters.

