demographic data (sex and age),eligibility (inclusion and exclusion criteria),caregiver verbal consent,the clinician's seniority and their perceived likelihood of appendicitis on a Visual Analog Scale from 0 being “Extremely unlikely” to 10 being “Extremely likely” and whether this perceived likelihood was formed before or after investigations (bloods, imaging, or both),history of the presenting complaint (location of initial pain, duration of pain, highest pain score, highest reported temperature during this illness, right lower quadrant (RLQ) or right iliac fossa (RIF) pain on arrival to ED, pain migration to RLQ or RIF, progression of pain, gradual onset of pain, pain pattern, history of pain with walking, anorexia, nausea, vomiting, difficulty with micturition, pothole tenderness, family history of appendicitis, respiratory tract infection in last 2 weeks, and bowel habit), andexamination findings (RLQ tenderness, RIF tenderness, tenderness worst in RLQ, tenderness outside RLQ, presence of hop, cough, or percussion tenderness, degree of rebound tenderness, abdominal guarding, Rovsing sign, nature of bowel sounds, palpable abdominal mass, and abdominal rigidity).

Clinician management will proceed independently of study participation.

All data collected at sites will be transcribed to a REDCap (Research Electronic Data Capture; Vanderbilt University) database [66]. The following additional data will be collected from the patient's medical records: blood test results (white cell count, absolute neutrophil count, neutrophilia, and C-reactive protein), urinalysis (presence of leukocytes or nitrites), which will then allow the various CPSs to be automatically calculated in REDCap.

Between 30-60 days after the ED visit, the site research team will collect the following parameters in all eligible patients through a medical record review:

detailed demographics (postcode, Medicare status, race or nationality, and referral source),prehospital management,management and imaging were undertaken both pre-ED in the community and the study hospital,time-related data (times of triage, clinician evaluation, ED, and hospital discharge),duration of ED and hospital stay,admission status and specialty unit consultations, including intensive care admission,medication use in ED, including antibiotics and analgesia,related surgical and nonsurgical interventions,other significant pathology or adverse events, including mortality, anddisposition.

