It will also collect the following details: details of ongoing problems; the number of missed days of school or childcare; the number of days off work; types and numbers of medical reviews; additional medical diagnoses; need for and duration of ED stay and hospital admissions including investigations (with a review of the relevant medical record); and related surgical interventions. Any eligible participants whose parent or guardian consented for data access and collection but declined follow-up will have their data collected and analyzed, but will not be contacted for follow-up. If participants withdraw consent and discontinue participation in the study at any time, there will be no effect on their medical care or access to treatment. If a participant withdraws before completing the study follow-up period, any known reason for withdrawal will be documented in the database. All information already collected as part of the study will be retained for analysis, but no further efforts will be made to follow up or obtain additional information regarding the participant. As an observational study, there are no anticipated adverse events related to the research. During the follow-up contacts, if any medical issues are identified by research staff, they will be referred to the managing clinicians (for patients in hospital), or the site investigator (for questions during follow-up), who will refer, if required, the patient to their general practitioner or ED for review.

To minimize information bias, the calculation of the CPSs will be performed by the research team and not by the treating clinician. If the study participant is transferred from a nonstudy site to a study site, the data collection form will be completed by the initial treating physician at the study site; if the study participant is transferred from a study site to a second study site, this will ideally be completed by the initial treating physician at the first study site.

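### pARC is in the care pathway at the lead site during enrolment, so gestalt recorded there may not be an independent comparator for pARC in secondary aim 1(A)

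*Protocol article*

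**What the plan says.** All references are to the protocol article.

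- **pARC in care.** The Conclusion states that "Implementation of the pARC score in the clinical management pathway for suspected appendicitis at PCH ED has recently been established", following the feasibility study. No start date is given.
- **The site.** The Overview under Methods names PCH as lead site, and Study Setting and Population lists it among the ten recruiting EDs.
- **Timing.** Results: "This study received funding in July 2023 and started enrolment in August 2023". By October 2024, 1227 participants had been enrolled and followed up, "with recruitment and data collection expected to be completed by mid-2025".
- **Safeguard.** Follow-Up: "To minimize information bias, the calculation of the CPSs will be performed by the research team and not by the treating clinician".
- **Management and forms.** Patient Recruitment and Data Collection: "Clinician management will proceed independently of study participation". The treating clinician records the gestalt rating and the history and examination items, at the visit or retrospectively for missed cases. The form notes whether gestalt was formed before or after bloods or imaging. None of the items listed in the article asks whether a prediction score was known.
- **Use of gestalt.** Secondary aim 1(A) sets the scores against clinician gestalt, and the Discussion presents that comparison as a key strength. In Principal Findings, "we hypothesize the pARC score will likewise have higher diagnostic accuracy in our multicenter study compared to other published CPSs".

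**The concern.** A comparison of a score with clinician judgement is informative only if the judgement was formed without the score. Keeping the study calculation with the research team achieves this where clinicians have no other access to the score. At PCH the local pathway may provide that access, and the clinician working within it is the person who rates gestalt.

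If gestalt already contains pARC, comparing the two is partly a comparison of pARC with itself. The hypothesis makes this more relevant: if pARC has the highest AUC, the gestalt comparison that the Discussion stresses becomes pARC against gestalt. Pooling all sites and dates would mix possibly pARC-informed ratings with uninformed ones, and the Strengths and Limitations section does not mention it.

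**Working it through.** **1. The plan's own figures are not in dispute.** Cases with all scores calculable: 2400 × 0.5 × 0.3 = 360, leaving 1200 − 360 = 840 non-cases. The Hanley-McNeil variance is [A(1−A) + (n1−1)(a−A²) + (n0−1)(b−A²)]/(n1·n0), with a = A/(2−A), b = 2A²/(1+A), n1 = 360 and n0 = 840. Half-widths of 1.96·SE are 0.0160 at AUC 0.95 and 0.0321 at AUC 0.75, as stated. Power, Φ(Δ/SE_Δ − 1.96), with the correlation between the two AUCs taken as 0.35 to 0.50, is 86-93% for 0.80 v 0.85 and 93-97% for 0.90 v 0.94. This agrees with the stated >85% and >90%. None of these figures changes.

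**2. Does the pathway overlap with enrolment?** The article describes the pathway as already in place and, at submission in October 2024, describes recruitment as open until mid-2025. Enrolment still to be completed and followed up was 2400 − 1227 = 1173, or 1173/2400 = 48.9% of target. Overlap at PCH is therefore likely. It is not certain, because PCH's own closing date is not given.

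**3. Does the safeguard cover it?** The safeguard governs the study calculation, while the pathway governs what PCH clinicians use in care. Both statements can be true together, and when they are, the safeguard does not establish that a PCH clinician was unaware of pARC when rating gestalt.

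**4. How many children?** This requires assumptions. Take PCH's share as 10-30% and, in line with step 2, half of its children enrolled after the start: 2400 × 0.10 × 0.5 = 120 to 2400 × 0.30 × 0.5 = 360, or 5-15% of the cohort. An earlier start would raise these numbers.

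**5. How far could gestalt move?** Illustration only, with every input assumed: binormal ratings, true AUC 0.85 for pARC (P) and 0.80 for gestalt (G), correlation 0.5, prevalence 30%, 400,000 simulated patients. In affected children gestalt becomes (1−w)·G + w·P.

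| Affected share | w | Gestalt AUC | pARC − gestalt |
|---|---|---|---|
| 0% | – | 0.800 | 0.050 |
| 10% | 0.25 | 0.804 | 0.046 |
| 10% | 0.50 | 0.806 | 0.044 |
| 20% | 0.25 | 0.808 | 0.042 |
| 20% | 0.50 | 0.812 | 0.038 |
| 30% | 0.25 | 0.812 | 0.039 |
| 30% | 0.50 | 0.818 | 0.032 |
| 50% | 0.25 | 0.819 | 0.031 |
| 50% | 0.50 | 0.830 | 0.020 |

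The 5-15% from step 4 lies within the range from no effect to the 20% rows, so the loss is at most 0.050 − 0.038 = 0.012. The 50% rows would need half of all children to be post-pathway PCH children. In this model pARC's own AUC does not move.

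**The case against.** The case against a larger finding is strong, and most of it stands.

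- **A reader might infer that the article contradicts its own blinding.** It does not. No blinding or masking of clinicians is stated; the sentence concerns only who calculates the study scores, and a local pathway does not make it false. The statement that management is independent of participation means usual care, which may include a hospital pathway.
- **A reader might infer that PCH clinicians did know pARC when rating gestalt.** The article does not say who computes pARC in the pathway, at what step, or from what date. Only *may know* is supported.
- **A reader might infer that pARC's own result is contaminated or favoured.** The study scores are calculated automatically in REDCap from recorded variables, and histopathology is the main reference standard. Other routes remain: clinician-recorded predictors, who has surgery rather than follow-up, and the exclusion of antibiotics-only cases. These are secondary and unquantified, and several feed many scores at once. For aim 1(A) the mixing works against the pARC hypothesis.
- **The form already has a timing field.** Background says most scores combine clinical and laboratory findings. If pARC does (its item list is in an appendix not shown), ratings made before investigations preceded a complete pARC. The field is therefore a useful partial check, but it does not record whether pARC was known.
- **Scope.** This is a secondary aim and one documented site of ten. A by-site sensitivity analysis may also sit in an analysis plan not shown, so its absence from the article is no defect.

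What remains is that the article states a safeguard in one place and, in another, a fact that limits it at the lead site, without connecting the two.

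**Conclusion.** The point holds in a limited form. With pARC in the PCH pathway during the study's recruitment period, gestalt from PCH after the start date may not be an independent comparator for pARC in secondary aim 1(A), and the stated safeguard does not prevent this. The likely effect is to narrow the pARC-gestalt difference. The size cannot be derived from the article. Under the assumed 10-30% PCH share, with half of its children enrolled after the start, 120-360 children are involved and the illustrative loss is no more than about 0.012 of a 0.050 gap. The direction rests on pARC being the more accurate of the two and on clinicians giving it some weight. The primary validation aim and the sample-size figures are not called into question.

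**What to change.** 1. Record the date on which pARC entered the PCH pathway. It can be recovered even after enrolment closes.
2. For aim 1(A), repeat the pARC-versus-gestalt comparison without PCH children enrolled after that date, and report whether the conclusion changes. As a further check, examine ratings formed before and after investigations separately, using the existing field.
3. Optionally, repeat the ranking of the scores on the same reduced set.
4. Qualify the sentence in Follow-Up: calculation by the research team does not ensure that clinicians at PCH were unaware of pARC after the pathway start date.

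The cost is one date, one additional analysis and one sentence, with no change to care or sample size. The downside is fewer children in that analysis. If 5-15% are removed and cases and calculability are spread evenly, confidence intervals widen by about 1/√0.95 = 1.03 to 1/√0.85 = 1.08. At AUC 0.75 the half-width goes from 0.032 to roughly 0.033-0.035.
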